## Abstract

**Background:**

Traditional Chinese medicine (TCM) has a long history of use in breast cancer, but lacking systematic evidence to support its clinical benefits. In this study, we evaluated the prophylactic and therapeutic effects of moxibustion combined with decoctions for treating chemotherapy-induced myelosuppression (CIM) in early-stage breast cancer patients.

**Methods:**

This is a randomized controlled clinical trial single-blinded for TCM decoction but not moxibustion. Patients are equally divided into the control group without decoction and moxibustion treatment (control), the decoction+moxibustion group (MD), and the placebo+moxibustion group (MP), according to the following stratification factors: age (below 40s, 40s, 50s, and 60s or above), chemotherapy regimen (anthracyclines, taxanes, anthracyclines+taxane, and others), and chemotherapy strategy (adjuvant and neoadjuvant). The TCM decoction is Wenshen Shengbai Decoction. The anticipated sample size is 462 cases (154 cases in each group). All participants are expected to treat with chemotherapy and recombinant human granulocyte colony-stimulating factor (rhG-CSF). The primary outcomes include the proportion of patients with relief of leukopenia and/or neutropenia, the myelosuppression-associated serious adverse event including grade 3–4 leukopenia and/or neutropenia, and febrile neutropenia, and the dose of rhG-CSF. The secondary outcomes include chemotherapy adherence, stratified analysis, adverse reactions, quality of life by EORTC Breast-Cancer-Specific Quality of Life Questionnaire including EORTC QLQ-C30 (V3.0) and QLQ-BR23, TCM Constitution, and 3-year disease-free survival and overall survival. Baseline information including age, surgical approach, chemotherapy regimen and strategy, pathological stage, and molecular subtype will be recorded.

**Discussion:**

This will be the first randomized controlled trial to evaluate the efficacy of moxibustion combined with TCM decoction in treating CIM in early-stage breast cancer patients, aiming to standardize the TCM decoction and moxibustion method, thus providing evidence for its clinical benefit.

**Trial registration:**

chictr.org.cn ChiCTR-INR-16009557. Registered on 23 October 2016.

## Administrative information

Note: the numbers in curly brackets in this protocol refer to SPIRIT checklist item numbers. The order of the items has been modified to group similar items (see http://www.equator-network.org/reporting-guidelines/spirit-2013-statement-defining-standard-protocol-items-for-clinical-trials/).

## Introduction

### Background and rationale {6a}

Breast cancer is the most common malignant tumour in Chinese women, and its number of new cases and deaths accounts for 12.2% and 9.6% of the total globally [1]. Chemotherapy is one of the routine treatments for breast cancer [2–4]. For patients with early-stage breast cancer, dose-densed anthracycline combined with taxane regimens [5–7] or high-intensity chemotherapy [8, 9] is often recommended, yet such a combination regimen can cause acute cytotoxicity. While inhibiting tumour cell growth, it also kills haematopoietic cells and leads to significant myelosuppression, especially neutrophils [10]. Chemotherapy-induced myelosuppression (CIM) could lead to febrile neutropenia (FN), increase the risk of infection, and affect the survival of patients and thus usually results in the reduction in dose or even discontinuation of chemotherapy [11]. Therefore, the prevention and treatment of CIM are critical in breast cancer management.

At present, recombinant human granulocyte colony-stimulating factor (rhG-CSF) is commonly used in the prophylactic and therapeutic treatment of CIM [12–14]. rhG-CSF is a synthetic cytokine that promotes the proliferation, differentiation, and activation of neutrophils, mainly used for treating neutropenia after cytotoxic chemotherapy. rhG-CSF can significantly reduce the incidence of FN, shorten hospital stay, and reduce the use of intravenous antibiotics without affecting the efficacy of anti-tumour therapy [15, 16]. Prophylactic use of rhG-CSF is considered in patients with dosing reduction or delayed chemotherapy which may lead to an unfavourable prognosis [17–19]. Although the short-term effect of rhG-CSF is prominent, its rapid white blood cell boosting effect does not last long. Also, it may cause side effects such as bone pain, fever, spleen rupture, myelodysplastic syndrome (MDS), and acute myeloid leukaemia (AML) [20–23], which seriously upset the quality-of-life (QoL) and life expectancy of patients.

Nowadays, the value of traditional Chinese medicine (TCM) and moxibustion as a comprehensive treatment approach in breast cancer is getting well-recognized [24]. A large number of clinical observations and experimental studies have manifested that TCM decoctions can reduce surgical complication rate, promote postoperative physical recovery, attenuate chemotherapy toxicity, diminish the risk of recurrence and metastasis, and reverse drug resistance. Moxibustion has also demonstrated beneficial effects in preventing CIM in cancers [25]. However, the application of TCM decoctions and moxibustion on preventing and treating CIM in breast cancer remains controversy. First, there are a limited number of studies exploring the optimal TCM regimen and dose for breast cancer. Second, various means of TCM regimens are available, leading to a lack of consistency between studies. Third, the moxibustion method is not standardized. Last but not the least, there is a lack of randomized controlled trials to support the efficacy of moxibustion combined with TCM decoction in treating breast cancer patients.

## Objectives {7}

The present study aims to evaluate the efficacy of moxibustion combined with TCM decoction in treating breast cancer patients with CIM, in a randomized controlled setting. Through this study, we intend to establish a standardized TCM regimen and moxibustion method and provide evidence for the clinical benefits of moxibustion combined with TCM decoction, in compliance with current clinical practice guidelines.

## Trial design {8}

This study is a randomized controlled clinical trial single-blinded for TCM decoction but not moxibustion. Patients will be divided into groups by stratified randomized grouping. The stratification factors involve age (below 40s, 40s, 50s, 60s, or above), chemotherapy regimen (anthracyclines, taxanes, anthracyclines combined with taxane, and others), and chemotherapy strategy (adjuvant and neoadjuvant). All eligible patients are equally divided into the control group with no TCM decoction/moxibustion treatment (control), the TCM decoction combined with moxibustion group (MD), and the placebo combined with moxibustion group (MP). All participants are expected to treat with standard chemotherapy and rhG-CSF regimen. The detailed study flow is illustrated in Fig. 1. The clinical pathway of each participant is shown in supplementary figure 1. Patients or the public will not be involved in the design, or conduct, or reporting, or dissemination plans of our research.

**Fig. 1 Fig1:**
[figure not shown]
Study flow

## Methods: participants, interventions, and outcomes

### Study setting {9}

Patients will be recruited from Yueyang Hospital of Integrated Chinese and Western Medicine, Shanghai University of Traditional Chinese Medicine.

### Who will take informed consent? {26a}

Written, informed consent to participate will be obtained from all participants through their responsible physicians. Participating in the study is voluntary. Participants may withdraw at any time without any given reason and the course of treatment will not be affected.

### Additional consent provisions for collection and use of participant data and biological specimens {26b}

On the consent form, participants will be asked if they agree to use their data in our ancillary study. Participants will also be asked for permission for the research team to share relevant data with people from the university taking part in the research or from regulatory authorities, where relevant.

## Interventions

### Explanation for the choice of comparators {6b}

The control group is treated routinely without either TCM decoction or moxibustion. Both the MD and MP groups are treated with moxibustion. The MD group is additionally treated with TCM decoction, while TCM placebo is provided to the patients in the MP group.

The TCM placebo which is made of excipients and flavouring agents is used as a comparator. The packaging, shape, weight, odour, and colour of the placebo are identical to that of the Wenshen Shengbai Decoction. The placebo is manufactured by Jiangyin Tianjiang Pharmaceutical Co., Ltd., and is stored and provided to the patients by the Central Pharmacy of Yueyang Hospital.

### Intervention description {11a}

#### Moxibustion

##### Acupoints

Shenque (CV8), Qihai (CV6), Guanyuan (CV4), bilateral Zusanli (ST36), and bilateral Sanyinjiao (SP 6) acupoints were selected. The rationale for moxibustion acupoint selection, treatment course, and duration has been described in a previous review published by our team [25]. Shenque (CV8), Qihai (CV6), and Guanyuan (CV4) belong to Ren meridian and govern the essence, blood, fluid, and fluid of the whole body.

##### Justification of acupoints

In the Inner Canon of Huangdi, the relationship between breast and meridian was described. The Stomach Meridian of Foot-Yanming runs downward along the midclavicular line and cross Ruzhong. The Spleen Meridian of Foot-Taiyin arises from the stomach, ascends through the diaphragm, and enters the chest. The Liver Meridian of Foot-Jueyin ascends through the diaphragm, distributes in the costal and the hypochondriac regions, and curves around the nipple. The Kidney Meridian of Foot-Shaoyin runs into chest to meet with breast. The Ren meridian ascends along the anterior medial line to the Guanyuan and enters the chest. The Chong meridian runs along both sides of the umbilicus and spreads over the chest. Therefore, current doctors generally accept that women’s nipple belongs to liver, and breast belongs to stomach. Thus, breast disease has a close relationship with zang-fu of liver, kidney, spleen, and stomach, as well as meridians of Chong-Ren. Zusanli belongs to the Stomach Meridian of Foot-Yanming and plays a role in assisting digestion, regulating spleen and stomach, reinforcing weakness, and regulating Qi and blood. Sanyinjiao originating from the postnatal essence belongs to the Spleen Meridian of Foot-Taiyin. It is the main intercept of the liver, spleen, and kidney meridians, which can strengthen the spleen and blood and regulate the liver and kidney [26]. Shenque, Qihai, and Guanyuan belong to the Ren meridian originating from the uterus, supervising the essence, blood, and body fluids from the whole body. Guanyuan is the chamber for essence and blood. Moxibustion of the Guanyuan acupoint can invigorate the kidney and Yang, regulate the Chong and Ren meridians, and harmonize Qi and blood [26]. Qihai is closely associated with the Qi of lung and is a key to the body’s Qi mechanism. Moxibustion of the Qihai can regulate the Qi mechanism and improve body health. Shenque is a key acupoint connecting to the whole body. It warms up the original Yang and runs the Yang-qi from the whole body. Therefore, the selection of the above acupoints considered to reinforce both the inborn and acquired conditions, aiming to warm up the kidney and Yang, adjust the essence, and nourish the blood.

##### Methodology

Fully expose the acupoints with mild moxibustion method, that is, ignite the moxa sticks, and then apply them to the acupoints. Cut a 1.5-cm-long moxa stick (ensure that the size and density meet the required specifications). The ignited moxa sticks should remain about 2–3 cm away from the skin to allow the patient to feel warm, but not burning (local skin should not appear red). The patient should be lying down, and the three acupoints including Shenque, Qihai, and Guanyuan should simultaneously apply moxibustion. Next, the patient should be sitting down, and Zusanli (both sides) followed by Sanyinjiao (both sides) should apply moxibustion. Each moxibustion lasts for 15 min. Gently massage the acupoints after moxibustion. The moxibustion should be performed once daily.

##### Course of treatment

Moxibustion starts from the 2nd day after chemotherapy and continued daily moxibustion until the day before the next cycle of chemotherapy. No moxibustion was given on the day of drug administration. The treatment course is completed 3 weeks after the end of the last chemotherapy. Daily self-moxibustion is carried out by the patient at home and is guided by Yueyang Hospital and Shanghai Acupuncture and Meridian Research Institute. Shanghai Research Institute of Acupuncture and Meridian will provide technical support for moxibustion.

#### TCM decoction

##### Prescriptions

Wenshen Shengbai Decoction consists of *Astragalus*, *Codonopsis pilosula*, *Atractylodes macrocephala*, *Poria cocos*, *Adenophora tetraphylla*, *Lycium chinense,*
*Epimedium*, *Cistanche deserticola*, *Morinda officinalis*, *Curcuma zedoaria*, *Salvia chinensis*, *Sophora flavescens*, *Rhizoma polygonati*, *Cornu cervi*, and *Psoralea corylifolia* [27]. The herbs are boiled and extracted into granules. It is orally administrated daily from the seventh day of each cycle of chemotherapy to the first day before the next cycle of chemotherapy, aiming to avoid the acute gastrointestinal reaction. The same amount of granules is put into the same container with 50-mL warm water. Stir until the particles are completely dissolved, and then add an appropriate amount of water to dilute. The granule is made by Jiangyin Tianjiang Pharmaceutical Co., Ltd., and is stored and provided to the patients by the Central Pharmacy of Yueyang Hospital.

##### Rationale of TCM decoction

Post-operative CIM in breast cancer often causes fatigue, dizziness, and unwillingness to speak, palpitations, insomnia and dreaminess, spontaneous sweating and tachypnea, pale and enlarged tongue, weak pulses, etc. Although the concept of myelosuppression was not mentioned in ancient TCM, these clinical symptoms could be classified as a kind of “blood deficiency” and “consumptive diseases”. The treatment of CIM should, therefore, base on the concept of “tonifying the deficiencies” and “warming the consumptions”.

The *Astragalus*, *Codonopsis pilosula*, *Atractylodes macrocephala*, and *Poria cocos* in Wenshen Shengbai Decoction can tonify Spleen and support Qi and secure the postnatal condition, thus activating Qi and developing blood; *Adenophora tetraphylla* and *Lycium chinense* can nourish Yin and promote body fluid; *Epimedium, Cistanche deserticola, and Morinda officinalis* can tonify the kidney, regulate Chong Ren, and constrain the prenatal condition, thus enhancing the healthy Qi and resistance to pathogenic factors; *Curcuma zedoaria* and *Salvia chinensis* can promote blood circulation and detoxification and resolve phlegm; *Sophora flavescens* can clear away heat and dampness; *Rhizoma polygonati*, *Cornu cervi*, and *Psoralea corylifolia* can tonify kidney and fill the essence.

#### rhG-CSF

The rhG-CSF is performed according to the guidelines [12–14]. Patients with grade 1 myelosuppression according to the CTCAE 4.0.2 criteria are follow-up for both the intervention group and the control group. Patients with grade 2 or above myelosuppression should receive rhG-CSF treatment until the WBC count and ANC return normal. Two types of adjuvant chemotherapy regimens in breast cancer, namely ddAC-wP and TAC, can lead to a high risk of FN (incidence > 20%). According to the NCCN guidelines, prophylactic rhG-CSF treatment is recommended on day 2 or days 3 to 4 after chemotherapy. In detail, 5 mcg/kg is administrated per day until neutrophil count returns normal or nearly normal level, or long-acting rhG-CSF (PEG-rhG-CSF) is given on the second day after chemotherapy.

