### Outcomes {12}

#### Primary outcomes

Primary outcomes are as follows:
The proportion of patients with relief of leukopenia and/or neutropenia.The number and proportion of patients with relief of myelosuppression-associated SAE, defined as grade 3–4 leukopenia and/or neutropenia and FN.The median and mean duration time of relief of leukopenia and/or neutropenia.The dosing of rhG-CSF.

The grading of adverse reactions is in accordance with the CTCAE 4.0.2 criteria. Leukopenia is defined as an abnormal decrease in white blood cells of less than LLN-3.0 × 10^9^/L. Neutropenia is defined as an abnormal decrease in netrophils of less than LLN-1.5 × 10^9^/L. The definition of FN is based on the IDSA guidelines (American Society of Infectious Diseases Guide 2010 edition), which is an absolute neutrophil count (ANC) of < 500 neutrophils/mcL or an anticipated decline to ≤ 500 in the next 48 h and progress to ≥ 38.3 °C orally or ≥ 38.0 °C for a duration over 1 h.

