### Sample size {14}

In previous studies, the incidence rate of myelosuppression was 81.0% in the control group and 61.7% in the TCM decoction group [29]. The cure rate and effective rate of the moxibustion group were 84.1% and 66.4%, while those of the control group were 35.2% and 33.3% [30]. In our preliminary study, the bone marrow suppression rate (grade 2 or above) was 52% and 81% for the MD group and the control group, respectively (δ = 15%in superiority trial). Since there are no previous data supporting the combination use of moxibustion and TCM decoction, the sample size calculation was simply based on MD/MP group versus control group, assuming that the effect of combination treatment is equivalent to or better than moxibustion or decoction alone. Considering patient enrolment at a ratio of 1:1:1 for the control, MD, and MP groups, the sample size is calculated by multiple sample rate comparisons. The sample content estimation formula is as previously described [31]. Given that *α* = 0.05 and 1-*β* = 0.08, taking a 20% drop rate into account, the required total sample size is 462 cases and 154 cases in each group.

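### Physicians who know the arm can vary how prophylactic rhG-CSF is given on ddAC-wP and TAC, while rhG-CSF dosing is a primary outcome

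*Protocol article*

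**What the plan says.** The rhG-CSF section opens with a general standard: "The rhG-CSF is performed according to the guidelines". Trial design {8} extends it to every arm: "All participants are expected to treat with standard chemotherapy and rhG-CSF regimen". The therapeutic rule is fairly tight: "Patients with grade 2 or above myelosuppression should receive rhG-CSF treatment until the WBC count and ANC return normal".

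The prophylactic rule in the same paragraph is looser. It follows from two regimens, "namely ddAC-wP and TAC, can lead to a high risk of FN". For these, "prophylactic rhG-CSF treatment is recommended on day 2 or days 3 to 4 after chemotherapy". The daily product is given at 5 mcg/kg "until neutrophil count returns normal or nearly normal level, or long-acting rhG-CSF (PEG-rhG-CSF) is given" on the second day. No numeric stop count, no PEG dose and no rule for choosing among the alternatives is printed.

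Primary outcomes lists "The dosing of rhG-CSF" as an outcome in its own right, and the abstract does the same. Sequence generation {16a} sends the allocation to the physicians in envelopes. Implementation {16c} has them enrol and assign patients. Who will be blinded {17a} says outcome assessment is not blinded to them. The control arm receives neither moxibustion nor placebo, so it is visibly open.

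**The concern.** Part of a primary outcome is set directly by people who know the arm. Each extra day of daily prophylaxis adds to the recorded rhG-CSF dose, whatever the patient's marrow is doing. A physician could follow the text faithfully and still start earlier, stop later or choose another product in one arm than in another. A lower dose under moxibustion would then have two explanations, less myelosuppression or different prophylactic habits, and a total dose alone could not separate them.

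The direction is not the same for all outcomes. Longer prophylaxis in the control arm would raise the control dose, which favours moxibustion. It would also tend to lower control leukopenia and neutropenia, which works against moxibustion.

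**Working it through.** No figure in the protocol article depends on this point, so there is none to reproduce. The check sets the texts side by side and then sizes one extra dose.

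**What is open once the arm is known.** Regimen class is a stratification factor (Trial design {8}), and Table 3 ticks chemotherapy regimen at baseline, so the regimen is normally chosen before allocation. How prophylaxis is then given stays open:

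- Start day: open for the daily product; fixed at the second day for PEG.
- Product: daily or PEG, with no rule.
- Stop point: a loosely described count for the daily product; not applicable to PEG.

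**Scope.** The Chemotherapy regimen section lists 2 anthracycline, 2 taxane, 5 combined and 4 other regimens: 2 + 2 + 5 + 4 = 13. Two of them, ddAC-wP and TAC, are tied to prophylaxis. Both sit in the combined class with three other regimens.

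**Size of one extra daily dose.** Inputs:

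- 5 mcg/kg per daily dose (rhG-CSF section).
- s, the share of patients on ddAC-wP or TAC. Not in the document; assumed 10% to 40%, middle value 24%.
- p, the share of these patients on PEG. Not in the document.
- d, the mean number of extra daily doses per cycle in one arm, among those on the daily product. Not in the document.

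Added dose per randomised patient per cycle in that arm = 5 × s × (1 − p) × d.

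With p = 0 and d = 1 (every such patient in one arm gets one extra dose every cycle, none in the other arm does, and nobody uses PEG):

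- s = 0.10: 5 × 0.10 = 0.5 mcg/kg
- s = 0.24: 5 × 0.24 = 1.2 mcg/kg
- s = 0.40: 5 × 0.40 = 2.0 mcg/kg

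With half on PEG and a mean gap of half a day (p = 0.5, d = 0.5), each figure falls to a quarter: 0.125, 0.30 and 0.50 mcg/kg. The result is proportional to d. A two-day gap (day 2 against day 4 with the same stop day) would double the first set, but because dosing stops on a count, a later start need not mean fewer doses.

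**Rough scale only.** Sample size {14} reports that "the bone marrow suppression rate (grade 2 or above) was 52% and 81% for the MD group and the control group, respectively", a difference of 81 − 52 = 29 points. Suppose, beyond what the document says, that each affected patient has one therapeutic course of 3 to 5 days at 5 mcg/kg per cycle. The therapeutic-dose difference is then 5 × 0.29 × 3 = 4.35 to 5 × 0.29 × 5 = 7.25 mcg/kg, or 5.8 at 4 days. The p = 0, d = 1 figures are 0.5/7.25 = 7%, 1.2/5.8 = 21% and 2.0/4.35 = 46% of it. The softer middle case is 0.30/5.8 = 5%. The document does not say that the 81% and 52% are per cycle, and fewer therapeutic courses would raise these percentages, so they serve only for orientation.

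**Product choice.** This cannot be sized. No PEG dose is printed, and a single PEG injection is not on the scale of mcg/kg per day.

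**The case against.** The strongest reply is that one standard already covers all arms. rhG-CSF follows guidelines, and the alternatives are presented as the guideline's own. A condensed article also commonly leaves product dose and numeric stop counts to the full protocol. This stands in part: a missing PEG dose or count is not a fault in itself. It does not dispose of the point, because the recommendation as restated contains the alternatives, and keeping to it does not prevent different use by arm.

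Three further replies stand as limits. Only 2 of 13 listed regimens are directly affected. The therapeutic rule, which applies to all participants, is much tighter. Any PEG use shrinks the start and stop exposure.

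A reader might infer more: that physicians did treat the arms differently, that the share given prophylaxis differs between arms, or that the leukopenia and neutropenia results are shifted by a known amount. The document supports none of these. It reports no rhG-CSF use by arm, no uptake, no share on the two regimens and no effect of prophylaxis on cytopenia. Any such figure would size an assumed gap in whether prophylaxis is given, whereas the printed looseness concerns how it is given.

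**Conclusion.** The point holds in a limited form. For patients on ddAC-wP or TAC, physicians who know the arm may choose the start day, the product and, for the daily product, a loosely defined stop point, while rhG-CSF dosing is a primary outcome. A between-arm dose difference could therefore partly reflect prophylactic practice.

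That this occurs is not shown, and its true size is unknown. For one extra daily dose per cycle, the effect is at most 0.5 to 2.0 mcg/kg per randomised patient per cycle. That rests on an assumed 10% to 40% share on these regimens, every such patient in one arm affected, and no PEG use; relaxing either of the last two lowers it. The point is worth acting on because the remedy is cheap. It is a cheap improvement and does not put the trial's validity in question.

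**What to change.** For patients still to be enrolled (462 − 218 = 244 at the last count in Trial status), record before the envelope is opened the exact regimen and the intended prophylaxis: yes or no, daily or PEG, start day, and a numeric ANC at which daily dosing stops. Follow that plan whatever the arm. The clinical content is for the sponsor's clinicians.

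For all patients, analyse and report prophylactic and therapeutic rhG-CSF dose separately by arm, with daily and PEG products kept apart. List departures from the recorded plan where one exists.

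Two other remedies are not advised. Adjusting for ddAC-wP or TAC handles a baseline factor and cannot remove choices made after allocation. Mandating a single product in mid-trial would be a treatment amendment and is not needed.

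The cost is a short form entry, slightly less freedom to change prophylaxis after allocation, and one extra table. The sample size does not change.
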